### Study Procedures

After enrollment in the study, patients will be evaluated for DED by clinical research coordinators using the DEA01. A physician will diagnose DED using the *standard method* without checking *test method* results. Details regarding the *test method* and *standard method* are shown in Textbox 2.

*Test* and *standard method.*
**
*Test method*
**
Dry eye disease (DED) diagnosis based on the app-based Japanese version of the Ocular Surface Disease Index (J-OSDI) and maximum blink interval (MBI), using the DEA01Patients will respond to the app-based J-OSDI questionnaire and be measured using the app-based MBI on the DEA01. The J-OSDI questionnaire is used to evaluate the subjective symptoms of DED on a 100-point scale [43,44]. The MBI will be defined as the length of time that a patient can keep their eyes open before blinking [26]. The app-based MBI will be measured using the smartphone’s camera on the DEA01 and a visually confirmed MBI will be measured using a stopwatch.
**
*Standard method*
**
DED diagnosis using a paper-based J-OSDI and tear film breakup time (TFBUT)Patients will respond to the paper-based J-OSDI questionnaire and be measured using TFBUT [20]. The diagnosis of DED using the *standard method* will be based on 2016 Asian Dry Eye Society criteria, with positive subjective symptoms (J-OSDI total score ≥13) and decreased TFBUT (≤5.0 s) being used to diagnose DED [20]. Based on the diagnosis using the *standard method*, patients will be allocated to DED and non-DED groups.

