### Data Collection and Outcome Assessments

The data collection items are shown in Textbox 3. The assessments will be done according to a predetermined sequence. First, the assessment of subjective symptoms of DED using the app-based J-OSDI and MBI on the DEA01 will be conducted as the *test method* by trained clinical research coordinators. The physician will not be informed of the *test method* results. The physician will then perform clinical examinations for DED, using the *standard method* and ophthalmic examinations. Clinical examinations for DED will include an evaluation of subjective symptoms of DED using the paper-based J-OSDI questionnaire, slit lamp–based MBI, TFBUT, corneal fluorescein staining (CFS), and tear secretion volume using Schirmer test I. The ophthalmic examinations will include measurement of visual acuity, intraocular pressure, and slit-lamp microscopic photography. All examinations will be performed within one day.

Data collection.

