#### Schirmer Test I for Tear Secretion Volume

Schirmer test I will be performed without topical anesthesia after all other examinations. A Schirmer test strip will be placed on the outer one-third of the temporal lower conjunctival fornix for 5 minutes. The length of the moisture stain on the filter paper (in mm) will be recorded [47].

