Secondary outcomes 1 to 4 were set to evaluate the DED diagnosis accuracy of the *test method* compared with that of the *standard method*. Secondary outcome 5 was included to determine the cutoff value for the app-based MBI using ROC analysis for DED diagnosis. Secondary outcomes 6 and 7 were included to determine if MBI measurements could be used as a substitute for TFBUT measurements. Secondary outcomes 8 and 9 were set to evaluate the reliability and validity of the app-based J-OSDI. Secondary outcomes 10 to 12 were set to evaluate the validity of app-based and slit lamp–based MBIs. In secondary outcome 13, patients will answer the following questions: “I think it’s easy to operate this smartphone app,” “I can use this smartphone app by myself,” “I want to be tested using this smartphone app rather than being tested at a medical institution,” and “I will continue to use this smartphone app” [49,50]. Patients will answer these questions on a 5-point Likert scale (1, strongly disagree; 2, disagree; 3, neutral; 4, agree; and 5, strongly agree) [51]. Secondary outcomes 14 and 15 were set to evaluate the safety and stability of the DEA01. DEA01 failure is defined as something not working as expected. Adverse events comprise unexpected signs, symptoms, or diseases encountered during the clinical trial, regardless of whether they are related to treatment. If serious adverse events or failure occur, these will be referred to the Juntendo Hospital Certified Review Board, and appropriate treatments will be provided as needed.

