The secondary outcomes of the overall concordance rate, positive/negative predictive value, and positive/negative likelihood ratio will be calculated by comparing the DED diagnosis results from the *test method* with the results from *standard method* in a mixed matrix. The diagnostic performance of DEA01 will be evaluated through calculating the area under the ROC curve plotted from the sensitivity and specificity of the *test method*. The substitutability of MBI measurement for TFBUT measurement in DED diagnosis will be assessed using ROC curve analysis and through calculating the area under the ROC curve, using the cutoff value of the app-based MBI for TFBUT ≤5 seconds. The internal consistency of the app-based J-OSDI will be evaluated using factor analysis and Cronbach α coefficient, with α>0.70 considered an acceptable range [53]. Correlation and consistency will be evaluated using Pearson or Spearman correlation coefficients, an intraclass correlation coefficient, and Bland-Altman analysis. In each patient group, study patients’ backgrounds will be analyzed using a 2-tailed unpaired *t* test for continuous variables and a chi-square test for categorical variables. If a continuous variable does not clearly follow a normal distribution, it will be appropriately transformed to a logarithm and aggregated with the mean and SD or the median and IQR will be used as descriptive statistics. The operability and usability of the DEA01 will be evaluated in each group using the average score of the 5-point Likert scale responses to the operability and usability questions and the number of patients who answered better or worse than neutral using 2-tailed unpaired *t* and chi-square tests. For safety assessment, the frequency and rate of adverse events will be calculated for each group, and between-group comparisons will be performed using Fisher exact probability or chi-square tests.

A 2-sided level of significance will be set at 5%, and the confidence coefficient will be set at 95%, unless otherwise specified. Missing value completion will not be performed.

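### The adverse event outcome is meant to evaluate the DEA01, but the stated test compares DED with non-DED patients, all of whom use the app, so it cannot speak to app safety

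*Protocol article*

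**What the plan says.** Under Secondary Outcomes, the article lists DEA01 failure as item 14 and adverse events as item 15, and gives their purpose: "Secondary outcomes 14 and 15 were set to evaluate the safety and stability of the DEA01". The same section defines the events: "Adverse events comprise unexpected signs, symptoms, or diseases encountered during the clinical trial, regardless of whether they are related to treatment".

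Under Sample Size and Statistical Analyses, the safety analysis is a single sentence: "For safety assessment, the frequency and rate of adverse events will be calculated for each group, and between-group comparisons will be performed". The tests it names are Fisher's exact test or the chi-square test.

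The groups are set out under Study Procedures: "Based on the diagnosis using the *standard method*, patients will be allocated to DED and non-DED groups". Exposure to the app is described in the same place: "After enrollment in the study, patients will be evaluated for DED by clinical research coordinators using the DEA01".

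Under Data Collection and Outcome Assessments, the app session comes first and the physician's work follows, all on one day. That work includes "evaluation of subjective symptoms of DED using the paper-based J-OSDI questionnaire, slit lamp–based MBI, TFBUT, corneal fluorescein staining (CFS), and tear secretion volume", together with visual acuity, intraocular pressure and slit-lamp photography. On the last of the dry eye tests: "Schirmer test I will be performed without topical anesthesia after all other examinations".

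**The concern.** A safety comparison informs about a device when the compared groups differ in exposure to it, or when one exposed cohort is summarised on its own. The stated analysis does neither. It splits a fully exposed cohort by diagnosis and tests the split.

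A significant result would show that patients with DED report events more or less often than patients without. A non-significant result would show nothing about the app, whether its own event rate is nil or substantial. The rates themselves also mix two sources: a non-contact camera session, and a set of clinic examinations that includes dye instillation and a Schirmer strip.

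What is at stake is whether outcome 15 can be interpreted. The article says that, as of December 2022, the app had not been approved as medical device software in Japan, so a readable safety statement has some value.

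**Working it through.** **The plan's own figures.** The article gives no figure for the safety analysis. The only sample size figures concern sensitivity and specificity: 100 per group, raised to 110, hence 220. Formula (2) is not shown. Assuming p = 0.5, a half-width of 0.10 needs n = (1.96/0.10)² × 0.25 = 96.04, so 97 against the stated 100. Inflating 100 for 10% exclusions gives 100/0.90 = 111.1, so 112 against 110. These agree within 3% and are used below only as group sizes.

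**What the between-group test estimates.** Let the app cause an event in a proportion *a* of patients and the later examinations in a proportion *e*, independently. The probability of at least one event is

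P = 1 − (1 − a)(1 − e).

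The article gives no event rates, so every value here is assumed. With *a* and *e* equal in the two groups, each group's rate is:

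| App rate *a* | *e* = 1% | *e* = 5% | *e* = 10% | DED minus non-DED |
|---|---|---|---|---|
| 0% | 1.0% | 5.0% | 10.0% | 0 |
| 1% | 1.99% | 5.95% | 10.9% | 0 |
| 5% | 5.95% | 9.75% | 14.5% | 0 |
| 10% | 10.9% | 14.5% | 19.0% | 0 |

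The difference is zero in every row, so the test cannot tell an app with no events from one with events in 10% of patients.

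**If the groups respond differently.** Suppose the examinations cause events in 10% of DED and 5% of non-DED patients.
- With a = 0 in both groups, the difference is 10.0% − 5.0% = 5.0 points.
- With a = 10% in both groups, it is 19.0% − 14.5% = 4.5 points.

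The contrast is then non-zero, but it arises from the examinations and hardly moves with the app's rate.

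**What the per-group rates say.** Since P ≥ a, each rate bounds the app's own rate from above. The bound is useful when events are few and loose when *e* is large. With a = 1% and e = 10%, the reported rate is 10.9%, about 24 of 220 patients, against 0.01 × 220 = 2.2 patients with an app-caused event.

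**What a single-cohort summary would say.** For zero events in n patients, the upper limit of the two-sided exact 95% interval is 1 − 0.025^(1/n):
- n = 220: 1.66%
- n = 200 (the minimum in both groups together): 1.83%
- n = 110 (one group): 3.30%

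The fixed order, app first and physician second, makes it possible to identify events that start before the examinations. The stated analysis makes no use of it.

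**The case against.** The strongest reply is that this is a presentation choice about the last of 15 secondary outcomes in a one-day diagnostic study, and that the details lie in documents not shown. Several parts of it stand.

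- A reader might infer that no planned result describes the app's safety. The documents do not support that. DEA01 failure is specific to the app and serves the same stated purpose, and the group rates are rates in app-exposed patients that cap app-caused events. Adding the two group counts also yields the pooled proportion. However, failure is defined as malfunction rather than harm to the patient, and the pooled count still mixes app and examinations.
- A reader might infer that irritation from the dye or the Schirmer strip is bound to be counted. The definition is limited to unexpected events, and the article does not say whether such irritation is expected. It may be counted or not.
- A reader might infer that onset and relatedness are not recorded. The full protocol, the data management plan and the adverse event form are not shown, so this cannot be said. Collecting events regardless of relatedness is ordinary practice and is no fault.
- A reader might complain that the app's non-invasiveness goes untested. The stated objective is diagnostic accuracy, and non-invasiveness is not a hypothesis of the study.

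The appeal to unseen documents does not remove the main point. The article does not leave the safety analysis open: it names the rates, the comparison and the tests, and that comparison does not match the purpose given for the outcome.

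**Conclusion.** The point holds in a limited form. The stated DED versus non-DED test cannot evaluate DEA01 safety, because both groups use the app in full. The rates by group give only an upper bound on app-caused events, because unexpected events from the later same-day examinations are included.

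The mismatch itself rests on the text and needs no assumed rate. The exact zero difference assumes equal app and examination effects in the two groups. Without that assumption the difference still does not isolate the app. The sizes shown for mixed rates are illustrations with assumed inputs. No passage says that a non-significant test would be taken as evidence of safety, so that misreading is a risk and not a plan.

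The impact is minor. Sensitivity, specificity, the MBI cutoff and the sample size are unaffected.

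**What to change.** In the safety sentence of Sample Size and Statistical Analyses:

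1. Make the DEA01 safety result a single proportion over all patients who used the app: those with an adverse event that starts before the physician's examinations or is judged related to the app, with an exact 95% CI.
2. Report events that start during or after the physician's examinations, and are not judged app-related, separately.
3. Keep the DED versus non-DED table as description and drop its significance test.

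If onset time and relatedness are already recorded, this is a change of wording only. If not, it needs one added field on the adverse event form. No extra patients or visits are required. The drawback is that a delayed effect of the app, appearing after the examinations have begun, is attributed only through a relatedness judgement.

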### Data Management

Data management will be conducted at an off-campus data center designated by the Juntendo University Certified Review Board in accordance with a preprepared data management plan. Data will be collected and linked at several points in time. Following database locking, locked data will be transferred to the person responsible for statistical analysis.

## Results

This study will start on February 1, 2023, at 3 medical institutions in Japan. Patient enrollment is expected to begin on February 1, 2023, and will end on July 31, 2023. Data will be analyzed in August 2023, and the results will be reported from December 2023 onward.

## Discussion

A recent report suggested that a significant portion of patients with DED might currently be left undiagnosed and experiencing a preventable decrease in QoL [13]. For those who are appropriately diagnosed, barriers to receiving care remain, including limitations related to employment, education, and the ongoing COVID-19 pandemic. Hence, there is a need for a nonintrusive, telehealth-based alternative to current in-person evaluations. In this study, the capabilities of a smartphone app-based diagnostic assistive device will be investigated in a multicenter, open-label, prospective, and cross-sectional study. The results are intended to demonstrate the reliability and validity of the DEA01 as a noninvasive tool to facilitate a diagnosis of DED, through determining the appropriate MBI cutoff value. Confirmation of the value of the DEA01 is likely to facilitate early intervention and greater outreach to undiagnosed populations with DED.

The health care paradigm is rapidly shifting to promote remote and online care given societal changes implemented during the ongoing COVID-19 pandemic [32]. Notably, for glaucoma- and diabetes-related retinopathy management, a new approach has been sought to monitor disease progression at home through the use of portable devices and to offer visits for ocular anomalies of concern [54]. This study aims to establish a new means to facilitate DED diagnosis in a nonintrusive, noninvasive manner using the DEA01 smartphone app, which can yield an objective metric for clinicians to evaluate remotely. This may lead to a global shift toward endorsing telehealth and thus, increasing accessibility and helping to remove barriers to health care. The potential to promote early diagnosis and intervention can dramatically affect disease prognosis on a global scale. Additionally, such apps are well aligned with the current paradigm shift away from standard facility-oriented care and toward a daily life–oriented longitudinal, human-centered health care approach [40,55,56].

The DEA01 is used to help assess subjective symptoms and collect objective findings through OSDI administration and MBI measurements, respectively. The reliability and validity of the MBI and OSDI in a remote setting to facilitate DED diagnosis have been previously shown through a previous DEA01 app designed for DED research, namely, DryEyeRhythm [31,32]. Additionally, discrepancies between results obtained from the standard paper-based OSDI and app-based OSDI have been previously shown to be acceptable [32]. Our prior study utilized the MBI cutoff derived from a slit-lamp microscopy–based MBI study [26]. This study aims to establish an MBI cutoff for smartphone app-based diagnosis assistance for DED. The establishment of an optimal MBI cutoff value will enable more robust and reliable app-based remote DED diagnosis assistance through the use of the DEA01.

In this study, the diagnostic performance utilizing the app-based MBI as a proxy for the standard TFBUT will be evaluated using the DEA01. TFBUT reflects tear film stability and homeostasis, acting as a critical component of DED diagnosis. However, it requires specialized tools and materials, including fluorescein dye and slit-lamp microscopy. Moreover, the invasive nature of the examination disrupts the in vivo status of the tear film and the ocular surface [20-23]. Some studies have shown that fluorescein dye results are not consistently reproducible and that the dye may negatively affect the stability of the tear film [57-59]. The MBI has been shown to have a positive correlation with TFBUT [26], suggesting that the MBI can be used as a noninvasive, nonintrusive metric to substitute for TFBUT. An online screening test, based on a patient’s self-measurement of the time from stopping blinking to feeling discomfort, has shown the utility of screening for DED detection [26,60]. However, the DEA01 may be more objective as it automatically measures the MBI using the sensors of a smartphone camera and allows for the evaluation of DED symptoms using the J-OSDI questionnaire. This study seeks to assess the viability of replacing TFBUT with app-based MBI measurements, which may enable remote, noninvasive, and nonintrusive diagnosis assistance concerning DED.

This study may have some limitations. First, this study may be affected by selection bias, as study patients are limited to those who have been evaluated in a highly specialized university hospital and those who are able to use the smartphone app [32]. Second, the study will be performed in a specific order. Patients will be required to first use the app, after which there will be a clinical evaluation for DED. This study sequence may be a confounder and might affect the results; therefore, assessing the effects of the examination order in a randomized study may be necessary [61]. Lastly, the DEA01 is designed to be an ancillary tool for initial DED diagnosis assistance, and specialized tests such as corneal staining and Schirmer test may be required to further assess disease severity and progression.

In conclusion, this study will evaluate the capability of the DEA01 in assisting a DED diagnosis. The study findings may potentially help to establish a noncontact, noninvasive, and remote consultation method for app-based DED diagnostic assistance using the mHealth DEA01 smartphone app. It is hoped that the DEA01 will provide effective diagnostic evaluation for DED in telemedicine and allow for early intervention in patients who have not been diagnosed with DED due to limited access to medical care.

## Abbreviations

CFS: corneal fluorescein staining
DED: dry eye disease
J-OSDI: Japanese version of the Ocular Surface Disease Index
MBI: maximum blink interval
mHealth: mobile health
OSDI: Ocular Surface Disease Index
ROC: receiver operating characteristic
TFBUT: tear film breakup time
QoL: quality of life
